#### Exploratory outcome measures

*Treatment toxicities* will be assessed by clinical nurses on a weekly basis during NACRT using the National Cancer Institute Common Toxicity Criteria for Adverse Events Version 3.0. *Treatment completion* will be assessed as the number of patients completing 100% of their planned radiation dose within 1 week of the planned completion date using electronic medical records. Additionally, the number of patients receiving ≥ 80% of their planned chemotherapy dose will be recorded. *Treatment response* will be assessed by pathologic complete response as reported by the pathologist after reviewing the surgical sample. *Surgical outcomes and complications* will be obtained from medical records.

#### Baseline descriptive variables

*Demographic variables* will be collected from the baseline questionnaire and will include age, sex, marital status, education, income, employment status, and ethnicity*. Behavioral variables* will include smoking and physical activity. Physical activity (PA) will be assessed using the GLTEQ [39]. All participants will complete the GLTEQ at baseline (PA in the past month), post NACRT (unsupervised PA in the exercise training group; all PA in the usual care group), and pre surgery (all PA in both the exercise training and usual care groups). *Medical variables* will be abstracted from medical records at baseline and will include disease stage, chemotherapy protocol, and ostomy. Comorbidities and a list of medications will be collected in the baseline questionnaire.

*Body composition/anthropometry* will be assessed by height, weight, and waist and hip circumference [40, 41].

### Sample size

Based on our feasibility study recruiting 18 patients in 6 months, we anticipate recruiting 60 patients over a 20-month period and randomizing 30 patients to each group. Based on this sample size, our study has 80% power, with a two-tailed alpha < 0.05, to detect a clinically meaningful effect of 3.5 ml/kg/min on our primary outcome of VO_2_ peak post NACRT, assuming a standard deviation of 5.6 ml/kg/min, 10% missing data, and adjustment for baseline value and other prognostic covariates [42]. This power may be sufficient for detecting differences in our secondary patient-reported outcomes if the effects are at least moderate (i.e., a standardized effect sizes of approximately ≥ *d* = 0.60). This power is unlikely sufficient for detecting potentially meaningful differences in any of the exploratory clinical outcomes. Given that the purpose of this phase II trial is to inform phase III trials, the patient-reported and clinical outcomes will be interpreted for potential clinical significance based on the direction and magnitude of numerical differences.

### Data analysis

We will use analysis of covariance (ANCOVA) at both the post-NACRT and pre-surgery time points to compare the two groups on all primary and secondary outcomes with adjustment for baseline value of the outcome as well as other potential covariates. All statistical analyses will be based on the intention-to-treat principle and include all patients with baseline and follow-up data. No missing data replacement strategies will be performed for this phase II trial as we anticipate < 10% missing data. Chi-square analyses will be used to explore between-group differences in the categorical and ordinal clinical outcomes. All analyses will be performed using SPSS (SPSS Inc., Chicago, IL, USA).

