### Randomization and blinding

After completing all baseline assessments, patients will be randomly assigned to either the exercise training group or usual care group in a 1:1 ratio using block randomization. A research assistant, not otherwise involved in the trial, will generate the block sizes and randomization sequence using a computer-generated random allocation sequence which will be concealed from the recruiting study coordinator. Given the nature of the intervention, it is not possible to blind the investigators or participants to group allocation. Additionally, due to logistical challenges at our facility, it is difficult to blind outcome assessors to group allocation for the primary outcome of cardiorespiratory fitness and the secondary outcomes of functional fitness. Nevertheless, fitness outcome assessors will follow a detailed protocol and be trained in the importance of standardizing outcome assessments and avoiding bias. Moreover, outcome assessors will not review the metabolic data during the cardiorespiratory fitness test, and the criteria for achieving peak volume of oxygen consumption (VO_2_ peak) will undergo an independent review. Finally, outcome assessors will be blinded to group assignment for the exploratory outcomes of treatment toxicities, treatment completion, treatment response, and surgical complications which will be assessed by medical staff not otherwise involved in the study.

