#### Feasibility and safety

The feasibility and safety of the exercise intervention will be determined based on eligibility rate, recruitment rate, exercise adherence rate, assessment rate, and adverse events. The willingness of rectal cancer patients to be randomized to a supervised HIIT program during NACRT is unknown; however, based on the results of our feasibility study, we anticipate a recruitment rate ≥ 50% [16]. Moreover, we do not know the willingness of patients in the usual care group to return for all follow-up assessments; however, based on the results of our feasibility study, we anticipate a follow-up assessment rate ≥ 80% at each time point [16].

Exercise adherence during NACRT will be assessed by the number of exercise sessions attended out of 18 as well as adherence to the workload and duration of the high-intensity intervals. Based on the results from our phase I study [16], we anticipate a median attendance rate to the supervised exercise training during NACRT ≥ 80%. Exercise adherence to the unsupervised exercise training after NACRT will be assessed by self-report using the Godin Leisure-Time Exercise Questionnaire (GLTEQ) [39]. Based on our previous results [16] we anticipate that the mean number of moderate-to-vigorous-intensity exercise minutes post NACRT will be ≥ 222 per week. Safety will be assessed by monitoring any serious adverse events that occur during exercise testing or the supervised exercise sessions. No serious exercise-related adverse events were observed in our previous study [16].

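### The primary analysis is called intention-to-treat but leaves out patients without follow-up, and the forecast that excuses having no missing-data method is not backed by the protocol's own follow-up figures

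*Protocol article*

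**What the plan says.** The Data analysis section plans a separate ANCOVA at the post-NACRT and pre-surgery visits, adjusted for the baseline value. It states that all analyses will be "based on the intention-to-treat principle and include all patients with baseline and follow-up data". It then rules out any handling of missing values and gives one reason: "No missing data replacement strategies will be performed for this phase II trial as we anticipate < 10% missing data".

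Three other places bear on that reason:

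- **Sample size** plans on 10% missing data.
- **Feasibility and safety** says it is not known whether usual-care patients will come back for every assessment, and continues: "we anticipate a follow-up assessment rate ≥ 80% at each time point".
- **Discussion** reports follow-up above 80% in the group's earlier single-arm study, in which every patient exercised.

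On timing, "After completing all baseline assessments, patients will be randomly assigned", so every randomised patient has a baseline treadmill test. Study design schedules fitness assessments again at post-NACRT and pre-surgery.

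**The concern.** A patient with no post-NACRT test contributes nothing to a post-NACRT ANCOVA. The analysis set is therefore the complete cases, and the label promises more than the rule delivers.

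This is not a detail left to an unseen analysis plan, because the protocol itself excludes any method. The exclusion rests on a forecast that no other section supports with data. The 10% in Sample size is an assumption, and nowhere is a follow-up rate of 90% or more given.

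Loss need not be harmless here. The primary test runs to exhaustion 0–7 days after chemoradiotherapy. The group's own feasibility work found side effects (88%), fatigue (76%) and diarrhea (71%) to be the commonest barriers to exercise in this period. Allocation is known to patients and to the fitness assessors. Unwell patients may skip the test, and the two arms may skip it for different reasons. If so, the primary contrast shifts, in a 60-patient trial meant to inform phase III.

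**Working it through.** **Inputs.** From Sample size: 30 per arm, difference 3.5 ml/kg/min, SD 5.6, two-sided 5%, 10% missing. From Data analysis: < 10% missing. From Feasibility and safety: follow-up ≥ 80%. From Recruitment: 18 patients in the earlier study.

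**1. What each rate allows**

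| Statement | Missing of 60 | Analysed per arm if even |
|---|---|---|
| < 10% missing | at most 5 | at least 27 |
| 10% missing | 6 | 27 |
| ≥ 80% followed | up to 12 | down to 24 |

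In the earlier study of 18, loss below 10% would require 17 or 18 assessed (17/18 = 94%). A rate reported only as above 80% does not establish that.

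**2. Power.** Normal approximation: power = Φ(δ / (σ√(2/n)) − 1.96).

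- Unadjusted, n = 27: 3.5 / (5.6 × √(2/27)) = 2.30, power 63%. The stated 80% therefore depends on covariate adjustment. The correlation r behind it is not given, so the 80% can only be back-solved.
- 80% at 27 per arm needs a residual SD of 5.6√(1 − r²) = 4.59, so r ≈ 0.57 (0.59 with the t distribution).
- Same r, n = 24: standard error 4.59 × √(2/24) = 1.325; 3.5/1.325 = 2.64; power Φ(0.68) ≈ 75%.
- Difference detectable with 80% power at 24 per arm: 2.80 × 1.325 ≈ 3.7 instead of 3.5.
- Over other r, power at 27 versus 24 per arm is 75.5% versus 70.5% (r = 0.5), 81.9% versus 77.2% (r = 0.6) and 89.5% versus 85.8% (r = 0.7).
- Keeping 54 analysable patients at 20% loss would take 54/0.8 = 67.5, so 68 randomised.

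**3. Bias of the planned ANCOVA.** The documents give no missing rates by arm and no fitness gap, so these are assumptions: SD 5.6; correlations 0.6 (baseline with post-NACRT), 0.6 and 0.7 for the remaining pairs; probability of a missing test depending logistically on post-NACRT fitness. A log-odds slope of 1 per 5.6 ml/kg/min reproduces the figures below.

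For an unadjusted mean difference, bias ≈ (m_E − m_C) × g, where m is the missing proportion in each arm and g the fitness gap between completers and missing patients. Baseline adjustment removes the part of g that baseline predicts and leaves about 1 − r² = 1 − 0.36 = 0.64 of it. At about 11% versus 21% missing, simulated unadjusted bias is −0.45 and 0.64 × 0.45 = 0.29, against −0.30 simulated for ANCOVA. At about 5% versus 25%, 0.64 × 0.92 = 0.59, against −0.61.

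| Missing, exercise vs usual care | ANCOVA bias (ml/kg/min) | Share of 3.5 |
|---|---|---|
| 13% vs 21% | about −0.17 to −0.25 | 5–7% |
| 10% vs 20% | about −0.30 | 9% |
| 5% vs 25% | about −0.6 | 17% |

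The negative sign follows from placing the larger loss in usual care, which shrinks the apparent benefit. With the larger loss in the exercise arm the sign reverses and the benefit is inflated.

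**4. What a longitudinal model recovers.** Fitted to all 60 in the same settings, with half of those missing the post-NACRT test returning before surgery, a repeated-measures model recovers about 0.04–0.13 ml/kg/min of bias and 2–3% of the standard error. In one run the mean estimate moved from 3.33 to 3.42 against a true 3.5. The rest remains because the model assumes missing at random, while missingness here depends on the unobserved value.

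**The case against.** The strongest reply is that nothing here is contradictory and the harm is small.

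- **The rates.** A reader might infer that the two forecasts conflict. They do not: 80% is a floor, loss below 10% satisfies it, and Sample size (10%) and Data analysis (< 10%) nearly agree. This stands. What remains is that a floor of 80% cannot serve as the reason for having no method.
- **Validity.** Complete-case ANCOVA is unbiased if missingness depends only on arm and the adjusted covariates. True, but the protocol gives no ground for expecting that with this test at this time.
- **Size.** A bias of 0.2–0.3 is small beside a standard error of about 1.25, and the longitudinal model recovers only part of it. This stands, and it limits the grade. Multiplying the raw fitness gap by the difference in missing rates would suggest more, but that describes unadjusted means and overstates the planned analysis about 1.5-fold (1/0.64 ≈ 1.56).
- **Direction.** A reader might take bias as certain, or as always conservative. No section says who will miss the test. Controls may not return, while the Discussion notes that exercising patients perceived possible worsening of fatigue and diarrhea.
- **Pathologic complete response.** A reader might infer that the same rule drops unresected patients from this outcome. The protocol says only that it is assessed "as reported by the pathologist after reviewing the surgical sample". It sets no denominator, the outcome has no baseline value, and it is exploratory. That extension is not supported.

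**Conclusion.** The point holds as a should-fix. The intention-to-treat label does not match the set analysed, and the sole reason for excluding any missing-data method is a forecast that the protocol's own follow-up figures leave unsupported.

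The likely damage is modest: about 5–17% of the target difference in the scenarios shown, in either direction, and about five points of power if follow-up is at its floor in both arms. The bias figures rest on assumed arm-specific loss, correlations and fitness-dependent missingness. The power figure rests on a back-solved correlation of about 0.57–0.59. If loss proves small and balanced, the effect will be small, but that cannot be known at the planning stage.

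**What to change.** 1. Call the current set complete-case, or modified intention-to-treat, in Data analysis.
2. Use one missing-data rate in Feasibility and safety, Sample size and Data analysis, and delete the < 10% forecast as the reason for having no method.
3. Fit a likelihood-based repeated-measures model to all randomised patients: VO2 peak at baseline, post-NACRT and pre-surgery as outcomes, a common baseline mean, arm-by-time effects after baseline and unstructured covariance (SPSS MIXED). Make its post-NACRT contrast primary, or at least a prespecified companion to the ANCOVA. State that it assumes missing at random.
4. Add one delta-adjusted (tipping-point) analysis with deltas varied separately by arm, since the model alone does not remove outcome-dependent bias. For scale, a delta of 3.5 applied to 20% of one arm moves that arm's mean by 0.20 × 3.5 = 0.7 ml/kg/min, one fifth of the target; at 10% it is 0.35.

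The cost is some rewording and a little programming in the software already named. No new patients or measurements are needed. The gain from step 3 is small, so steps 1, 2 and 4 matter at least as much.

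### The protocol names chi-square for ordinal clinical outcomes; on the ordinary reading this ignores toxicity grade order and gives no direction or size of effect (low severity, cheap to improve)

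*Protocol article*

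**What the plan says.** The Data analysis section gives a single method for the clinical endpoints: "Chi-square analyses will be used to explore between-group differences in the categorical and ordinal clinical outcomes". It names no rank test, trend test or ordinal model.

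The Exploratory outcome measures section lists the endpoints:

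- Toxicity: it "will be assessed by clinical nurses on a weekly basis during NACRT using the National Cancer Institute Common Toxicity Criteria for Adverse Events Version 3.0". This is the one clearly graded outcome. The article does not say how weekly records become one value per patient or how many grades will be compared.
- Radiation completion is the "number of patients completing 100% of their planned radiation dose within 1 week of the planned completion date", which is binary.
- For chemotherapy, "the number of patients receiving ≥ 80% of their planned chemotherapy dose will be recorded", which is also binary.
- Treatment response "will be assessed by pathologic complete response as reported by the pathologist after reviewing the surgical sample", again binary.
- Surgical outcomes and complications come from medical records, with no scale stated.

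The Sample size section concedes that "This power is unlikely sufficient for detecting potentially meaningful differences in any of the exploratory clinical outcomes". It adds that patient-reported and clinical outcomes will be judged by which way the numbers differ and by how much.

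**The concern.** The sentence acknowledges that some clinical outcomes are ordinal and still gives them the same unqualified test as the categorical ones. This is a stated choice of method, not a detail left for the analysis plan.

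Two things are at stake. First, an ordinary chi-square on a table of arm by grade answers only whether the two distributions differ somewhere. It does not say whether toxicity is milder or worse with exercise, or by how much, and that is how the Sample size section intends to read the result. Direction matters here: the Discussion reports that phase I patients perceived possible worsening of fatigue, diarrhea, skin irritation and hand-foot syndrome. Second, if exercise shifts toxicity fairly evenly along the scale, ignoring the order gives up power that the trial has little of.

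**Working it through.** **Inputs from the protocol.** There are 30 patients per arm ("we anticipate recruiting 60 patients over a 20-month period and randomizing 30 patients to each group"). The two-sided 5% level is the one stated for the primary outcome. Allowing for the 10% missing data assumed in the Sample size section leaves 0.9 × 30 = 27 per arm.

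**The plan's own figure.** None bears on this point. The only stated power, 80%, is for VO2 peak; no power is given for any ordinal outcome.

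**Step 1: why order drops out (no assumptions needed).** With equal arms and counts a_k and b_k in grade k, the ordinary statistic is X² = Σ (a_k − b_k)² / (a_k + b_k) on K − 1 degrees of freedom. Each grade enters as a separate term without its rank, so relabelling the grades leaves X² and its p value unchanged. The differences are squared, so no sign survives. The Wilcoxon and trend statistics use the rank or score of each grade and have one degree of freedom.

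**Step 2: assumptions for the power comparison.** The article gives no grade distribution or effect size, so these are assumed. A benefit with odds ratio OR multiplies each cumulative odds by OR. For example, with usual-care grades of 15/30/30/20/5% the cumulative proportions are 0.15, 0.45, 0.75 and 0.95. Doubling the odds gives 0.261, 0.621, 0.857 and 0.974, so the exercise arm has 26.1/36.0/23.6/11.7/2.6%.

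**Step 3: simulation.** 20,000 trials per setting, 30 per arm, two-sided 5%. Entries are power for ordinary chi-square against tie-corrected Wilcoxon.

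| Assumed usual-care distribution (%) | OR 2 | OR 3 | OR 4 |
|---|---|---|---|
| 5 grades, 15/30/30/20/5 | 17 v 31 | 40 v 64 | 61 v 83 |
| 5 grades, skewed, 50/25/15/7/3 | 14 v 27 | 31 v 54 | 46 v 71 |
| 6 grades, 10/25/30/20/10/5 | 15 v 31 | 35 v 64 | 56 v 84 |
| 6 grades, skewed, 55/12/15/10/6/2 | 11 v 26 | 24 v 51 | 37 v 68 |
| 4 grades, 25/35/25/15 | 20 v 31 | 44 v 62 | 65 v 81 |
| 3 grades, 30/40/30 | 23 v 30 | 50 v 61 | 70 v 80 |

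The ratio of chi-square power to Wilcoxon power, over all settings tried:

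- five or six grades, OR 2 to 3: about 0.41 to 0.64
- five or six grades, OR 4 to 5: 0.55 to 0.82
- four grades, OR 2 to 5: 0.64 to 0.86
- three grades, OR 2 to 5: 0.78 to 0.92

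With 27 per arm the ratios are similar, 0.40 to 0.92 overall. The linear-by-linear trend test comes close to Wilcoxon, at most about 6 points lower when grades are skewed.

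**Step 4: analytic check.** Hold the noncentrality fixed and spread it over more degrees of freedom. A 1-df test with 50% power has noncentrality 1.96² = 3.84; the same value on 2, 3, 4 and 5 df (three to six grades) gives 40%, 35%, 31% and 28%. A 1-df test with 80% power has (1.96 + 0.84)², about 7.85; the same value gives 71%, 65%, 60% and 56%. The size and pattern agree with the simulation.

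**Step 5: where the rank test does worse.** Take usual care as 15/30/30/20/5% and 30 per arm. If exercise moves patients to both ends (30/15/15/30/10%), chi-square has 43% power and Wilcoxon 6%. If only the severe grades fall (15/40/40/5/0%), the figures are 33% and 23%.

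**The case against.** The strongest reply has four parts.

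- **The outcomes are exploratory.** Low power is conceded, the test is used only to explore, and no stated decision depends on its p value. This stands, and it keeps the severity low.
- **The wording is unqualified.** A chi-square for trend is not excluded, and the variant could be left to the analysis plan. A reader might infer that the Pearson test is specified; the article does not use that word. But one unqualified term covers categorical and ordinal outcomes alike, so the unordered test is the ordinary reading. If a trend test is meant, the sentence needs to say so.
- **Direction can be read from the counts.** It can, informally. That still leaves the graded outcome without a single estimate or interval, which is what a reading by direction and size needs.
- **The rank test is not always better.** This stands. Step 5 shows large losses when the shift is not uniform, and the Discussion's mix of perceived benefits and harms makes such a pattern possible. Changing the test therefore has a cost, and the grade distribution must be shown as well.

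A reader might also infer that small expected counts invalidate the chi-square. With the 15/30/30/20/5% distribution an expected count fell below 5 in at least 96% of simulated tables, yet the rejection rate under no effect was 4.3% (Wilcoxon 5.1%). That is slightly conservative, and no harm is shown.

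**Conclusion.** The point holds in a limited form. The protocol assigns chi-square to ordinal clinical outcomes. On the ordinary reading this ignores grade order and gives no direction or size, which sits badly with its own rule for interpreting these outcomes. That part rests on the text and the formula alone.

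The power loss rests on assumed grade distributions and a proportional-odds shift. A reader might infer that the test halves power in general. The documents do not support that: it fits only five or six grades with a modest shift, while with three grades the relative loss is 8% to 22%.

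The scope is also narrow. Toxicity is the only clearly graded outcome. Radiation completion, the 80% chemotherapy count and pathologic complete response are binary, and on a 2 × 2 table the chi-square and trend tests practically coincide. The 80% chemotherapy cut is a prespecified binary endpoint; wanting a continuous version beside it is a preference, not an error.

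Severity is low: a cheap improvement to an exploratory analysis.

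**What to change.** Replace the sentence in Data analysis with wording such as: *Graded clinical outcomes will be compared with the Wilcoxon–Mann–Whitney test (or the linear-by-linear trend test) and summarised by a proportional-odds ratio with 95% CI; the number of patients in each grade will be tabulated by arm. Binary and unordered outcomes will be compared with the chi-square test, or Fisher's exact test when counts are sparse.*

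Fisher's test is likely to be relevant for pathologic complete response: at the 10–20% cited in the Discussion, 30 patients per arm give 0.10 × 30 = 3 to 0.20 × 30 = 6 expected responders per arm.

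The cost is a sentence or two in the plan, with no new data. The statistical price is lower power when exercise moves patients to both extremes or changes only part of the scale. The table by arm lets a reader see such a pattern, which a single odds ratio would hide.
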